### Study setting

The endoscopists participating in this trial are selected based on predefined criteria. With the knowledge that the operational difficulty of colon ESD is very high, a minimum prior number of procedures was defined in order to avoid that results will be biased by a learning curve. Based on the literature, 25 colorectal ESD-procedures is considered to be required to achieve expert experience [14–16]. Previous esophageal and stomach ESD experience alone will not be enough to ensure colorectal ESD expertise, as colorectal ESD is known to be technically more difficult than upper gastro-intestinal ESD due to the more challenging anatomical characteristics of the colon (thin wall, folds, peristalsis, angulated positions, and fecal fluid) [17]. This study will therefore only allow endoscopists that have performed >25 colorectal ESD procedures in the past three years to treat patients randomized to the ESD arm. In centers without ESD-experienced endoscopists, patients will be referred to an ESD-expert center when randomized to the ESD-arm. Patients randomized to the EMR arm will be treated by endoscopists which have extensive experience with EMR, defined as >500 prior EMR’s of which >50 in colorectal adenomas larger than 20 mm.

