Abbreviations: *CRC* colorectal cancer, *N* number of questions per item, *VAS* Visual Analogue ScaleHealth resources utilizations and costs at 36 months. Data on healthcare utilization will be gathered in the electronical case record form for instruments used, time needed to perform the procedure, admission to the ward and/or intensive care, length of hospital stay, (repeated) treatment or (prolonged) hospital stay for complications, used anesthesia and anesthesia staff, material and time needed for repeated treatment or (prolonged) hospital stay for recurrence and surgical referral. These data will be used to calculate healthcare costs.Surgical referral rate at 36 months. This is defined as the total number of patients that are referred for surgical management.Long-term recurrence rate at follow-up colonoscopy after 36 months. This will be observed from resected residual disease or, if not present, from biopsies of the post-polypectomy scar.Complication rate within 30 days after treatment. Intraprocedural perforation is defined as the condition in which the abdominal cavity is visible from the colorectal lumen during the procedure because of mural tissue defects, that requires (1) (prolonged) admission or (2) surgery. Intraprocedural bleeding is defined as bleeding that occurs during the procedure that is not controlled by electrocoagulation and/or hemoclipping, and that requires (1) transfusion or (2) termination of the endoscopic resection. Postprocedural bleeding is defined as bleeding within 30 days after the procedure resulting in (1) new presentation at the hospital, (2) hospital admission, or (3) repeated colonoscopy to obtain hemostasis. Postprocedural perforation is defined as perforation within 30 days after the procedure that is detected after completing of the procedure during which perforation did not occur, diagnosed by abdominal pain with focal guarding and a rise in C-reactive protein and/or fever (T >38.5 C) in combination with free air in the peritoneal cavity at abdominal CT-scan. Postprocedural serositis is defined as abdominal pain with focal guarding and a rise in C-reactive protein and/or fever (T >38.5 C) within 30 days after the procedure, but without signs of perforation (free air at abdominal CT-scan) and in the absence of another infection focus (urinary, pulmonary etcetera).

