Dose and type of sedation to be given is at the discretion of the endoscopist and will be registered. All colonoscopies will be performed with a high-resolution magnifying video-endoscope. A 0.9 % saline solution or succinylated gelatine together with dye will be used as the injection fluid. A circumferential incision will be made using a ESD-knife. The incision must be placed on a distance of 2-5 mm around the border of the polyp. This is because thermal damage otherwise makes it difficult to evaluate the histological resection margins after resection. A complete or partial circumferential incision is performed first and then further dissection is performed after the lesion is adequately situated. The endoscopist is allowed to perform the resection using the hybrid ESD (hESD) technique only as an escape method. This hESD technique consists of a circular incision around the lesion, with partial preparation in the submucosal layer that is sufficient to capture it with a snare in a single piece. Adjunct therapy with either tipping with the snare using forced coagulation (ERBE VIO 300; 25 W) or treatment with argon plasma coagulation (ERBE VIO 300; 60 W, 2.0 L/min) will only be performed when remnant tissue in suspected and must be registered.3.*Both arms*

For both procedures length of the procedure will be measured, defined as the total time needed for resection of the polyp, measured from the minute the injection fluid is injected until the endoscopist finishes final inspection of the resection wound and all specimen pieces are collected and removed.

For both procedures the opposite colonic wall of the resection site will be marked with India ink in case the adenoma is located in the sigmoid or descending colon, to ensure that the post-polypectomy scar can be found during follow-up.

For both procedures the following events are considered standard care, however, will be registered. In case intraprocedural perforation occurs, this will be treated using clips. In case of a minor bleeding from a small vessel, contact coagulation with the tip of a knife or coagulation with hemostatic forceps will be used for hemostasis. In cases of a severe bleeding from a large vessel or artery, hemostatic forceps will be used for hemostasis. If a pulsating large vessel is exposed within the resection wound, clipping can optionally be used to prevent delayed bleeding. If overnight admission is required, this will be registered including motivation.

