### Safety monitoring

The investigators will inform the subjects and the reviewing accredited medical ethics committee if anything occurs, on the basis of which it appears that the disadvantages of participation may be significantly greater than was foreseen beforehand. The study will be suspended pending further review by the accredited medical ethics committee, except insofar as suspension would jeopardize the subjects’ health. The investigators will take care that all subjects are kept informed.

Adverse events (AE) are defined according to the complication registration of the Dutch Society of Gastrointestinal Diseases (NVMDL) for non-severe complications [27]. Endoscopic resection related AE’s are: intraprocedural perforation, intraprocedural bleeding, postprocedural bleeding or postprocedural serositis that requires (prolonged) admission <10 days and/or maximum 4 units blood transfusion and/or endoscopic or percutaneous (re-) intervention. Serious adverse events (SAE) are defined as intraprocedural perforation, intraprocedural bleeding, postprocedural bleeding or postprocedural serositis or any other event with a possible or definite causal relation with the study intervention as judged by the treating physician that requires (1) > 10 days (additional) admission and/or (2) 4 units blood transfusion and/or (3) angiographic or surgical intervention and/or, (4) ICU admission and/or (5) death. These SAE’s will be reported to the accredited medical ethical committee of the University Medical Centre Utrecht (UMC Utrecht), within 15 days after the local investigator has first knowledge of the serious adverse events.

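### The postprocedural bleeding definition misses a bleed in a patient who is still admitted and is managed without repeat colonoscopy

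*Protocol article*

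**What the plan says.** Under Secondary outcomes, the article lists "Complication rate within 30 days after treatment" and then defines five complications. A bleed in the 30 days after the procedure counts if it is one "resulting in (1) new presentation at the hospital, (2) hospital admission, or (3) repeated colonoscopy to obtain hemostasis". The list is closed: nothing follows the third item.

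Two neighbouring definitions are worded differently. Intraprocedural perforation is one "that requires (1) (prolonged) admission or (2) surgery". Intraprocedural bleeding is bleeding not controlled by the usual endoscopic means "and that requires (1) transfusion or (2) termination of the endoscopic resection".

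Safety monitoring grades postprocedural bleeding together with other events. The adverse event class ends in "postprocedural serositis that requires (prolonged) admission <10 days and/or maximum 4 units blood transfusion and/or endoscopic or percutaneous (re-) intervention". The serious class lists, among other things, "1) > 10 days (additional) admission and/or (2) 4 units blood transfusion and/or (3) angiographic or surgical intervention", plus intensive care admission and death.

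Trial interventions foresees inpatients in both arms: "If overnight admission is required, this will be registered including motivation". Data analysis compares the complication rate between arms with a stratified test for a binary outcome. Recruitment and randomization states that patients and endoscopists are not blinded.

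**The concern.** Two of the three triggers describe a change of place: coming to the hospital, or being admitted to it. Neither can occur in someone who is already an inpatient. For that patient only the third trigger, a repeat colonoscopy, is left. Whether a bleed counts then depends partly on where the patient was when it happened and not on how serious it was.

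Two things are at stake. First, the rate is too low in both arms, and the missing events can include transfused bleeds. Second, the decision to keep a patient overnight is made with knowledge of the arm. If overnight stay is more common in one arm, more of that arm's bleeds fall into the gap, and the comparison of complication rates shifts in its favour. The Background presents complications as part of the price of ESD, so the safety comparison should not depend on discharge practice.

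**Working it through.** **Text check.** The table applies the three triggers as written to a bleed after the procedure.

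| Situation | New presentation | Admission | Repeat colonoscopy | Counted |
|---|---|---|---|---|
| Discharged, mild bleed, returns and is sent home | yes | no | no | yes |
| Day-care patient, bleed leads to admission | no | yes | no | yes |
| Already admitted, repeat colonoscopy | no | no | yes | yes |
| Already admitted, transfused or kept longer, no colonoscopy | no | no | no | **no** |
| Already admitted, straight to angiography or surgery | no | no | no | **no** |

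The last two rows are the gap. Safety monitoring uses exactly those consequences to grade postprocedural bleeding. On the plain wording, an inpatient bleed can be severe enough for the serious class and still be absent from the complication rate.

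**Size.** The article states no bleeding or admission rates, so there is no figure to reproduce and every input below is an assumption.

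- b = true rate of postprocedural bleeding, the same in both arms: 6% (range 4 to 10%)
- f = share of bleeds in the first night: 40% (30 to 50%)
- m = share of those managed without repeat colonoscopy: 50% (30 to 50%)
- s = share of patients kept overnight: ESD 70% (50 to 90%), EMR 20% (10 to 20%)

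Missed bleeds, as a share of all patients in an arm = b × f × m × s.

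Base case:
- ESD: 0.06 × 0.4 × 0.5 × 0.7 = 0.84%
- EMR: 0.06 × 0.4 × 0.5 × 0.2 = 0.24%
- Difference: 0.60 points, or 0.0060 × 106 = 0.6 of a patient per arm of 106

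Range by arm:
- ESD: 0.04 × 0.3 × 0.3 × 0.5 = 0.18% to 0.10 × 0.5 × 0.5 × 0.9 = 2.25%
- EMR: 0.04 × 0.3 × 0.3 × 0.1 = 0.04% to 0.10 × 0.5 × 0.5 × 0.2 = 0.50%

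Range of the net difference. Here b, f and m are common to both arms and only s differs, so the difference is b × f × m × (s in ESD − s in EMR):
- Smallest: 0.04 × 0.3 × 0.3 × (0.5 − 0.2) = 0.11 points, about 0.1 patients per 106
- Largest: 0.10 × 0.5 × 0.5 × (0.9 − 0.1) = 2.0 points, about 2.1 patients per 106

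If s is equal in both arms, the difference is zero: both arms are undercounted alike. If more EMR patients stayed overnight, the sign would reverse.

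**The case against.** The strongest objection is that the gap is narrow. An inpatient bleed that needs repeat colonoscopy counts, and so does a day-care patient's bleed that leads to admission. What drops out is a bleed before discharge, in a patient admitted for another reason, that is managed without colonoscopy. That is correct, and the point is confined to it.

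A reader might infer that the complication comparison is biased in favour of ESD. The documents do not support that. They give no overnight rates by arm. More stay after ESD is plausible: the Background cites procedures about three times as long and more perforations (5.7% versus 1.4%), and under Study setting, in centers without ESD-experienced endoscopists, "patients will be referred to an ESD-expert center when randomized to the ESD-arm". But those perforation rates come from retrospective studies, the same section expects a more favourable safety profile in the distal colon, and nothing is said about travel distance. In addition, if complications are counted per patient, missing a bleed in someone already counted for a perforation changes nothing. Bias in this direction is therefore possible, not shown.

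It can also be said that severe inpatient bleeds are not lost, because the serious adverse event definition includes a clause for any other related event of that severity. This protects safety reporting. It does not put the event into the complication rate that is compared between arms.

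One could read admission as including prolonged admission. That is strained, because the article writes out the prolonged case elsewhere, including in the same paragraph.

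Finally, an article condenses a fuller protocol, and the definition there may be wider. That excuses missing detail. Here the article gives a complete list that, followed as written, leaves events out.

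**Conclusion.** The point holds as a defect in a stated definition. As written, an inpatient bleed managed without repeat colonoscopy is not counted, while a milder bleed in a returning outpatient is. This is out of line with the neighbouring definitions and with the grading under Safety monitoring.

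The undercount in both arms follows from the text wherever such bleeds occur. A distorted arm comparison is conditional on overnight stay differing between arms. With the assumed inputs it is about 0.1 to 2.0 percentage points, at most about two patients per arm of 106. The primary endpoint and the sample size are untouched. Severity is minor to moderate: few events, but they can include transfused ones, in a safety outcome that the trial compares between arms.

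**What to change.** Keep the three existing triggers for postprocedural bleeding and add prolonged admission, transfusion, and angiographic or surgical haemostasis, so that the definition applies equally to patients at home and on the ward. Then reconcile the wording under Secondary outcomes with the grading under Safety monitoring, so that a bleed that qualifies for an adverse event class also counts in the complication rate.

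Bleeds that led only to a hospital visit can be shown separately as a descriptive breakdown. Taking them out of the complication rate is a matter of preference and is not needed to close the gap.

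The cost is one sentence in one definition. Treatment and prolonged stay for complications are already collected in the case record form for costing, overnight admission is registered with its reason, and transfusion is needed anyway to assign the adverse event classes.

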### Trial interventions

*EMR-arm*

Dose and type of sedation to be given is at the discretion of the endoscopist and will be registered. All colonoscopies will be performed with a high-resolution magnifying video-endoscope. A colloidal solution (such as succinylated gelatine) and dye will be used as the injection fluid, mixture with 1:100.000 adrenaline is optional. The purpose of this injection is to elevate the lesion away from the muscle layer, and to accentuate the plane of excision so that a wide and deep excision is achieved. Marking of the periphery of the polyp with coagulation is allowed to optimize the attempt of an en-bloc or R0-resection. A snare is then passed through the channel and opened around the lesion. The snare is snugged around the lesion and pulled. Cautery is applied to resect the lesion. Only when en-bloc resection is not feasible, the endoscopist is allowed to perform the resection in a piecemeal fashion (pEMR) in as less pieces as possible. The number of pieces will be registered. In case of pEMR, adjunct therapy with either tipping with the snare using forced coagulation (ERBE VIO 300; 25 W) or treatment with argon plasma coagulation (ERBE VIO 300; 60 W, 2.0 L/min) will be performed. This will be applied in short bursts to coagulate the entire edge of the polypectomy site. Any remaining tissue in the polypectomy site will also be coagulated. In case of en-bloc EMR, adjunct therapy with coagulation will only be performed when remnant tissue is suspected and must be registered.2.*ESD-arm*

Dose and type of sedation to be given is at the discretion of the endoscopist and will be registered. All colonoscopies will be performed with a high-resolution magnifying video-endoscope. A 0.9 % saline solution or succinylated gelatine together with dye will be used as the injection fluid. A circumferential incision will be made using a ESD-knife. The incision must be placed on a distance of 2-5 mm around the border of the polyp. This is because thermal damage otherwise makes it difficult to evaluate the histological resection margins after resection. A complete or partial circumferential incision is performed first and then further dissection is performed after the lesion is adequately situated. The endoscopist is allowed to perform the resection using the hybrid ESD (hESD) technique only as an escape method. This hESD technique consists of a circular incision around the lesion, with partial preparation in the submucosal layer that is sufficient to capture it with a snare in a single piece. Adjunct therapy with either tipping with the snare using forced coagulation (ERBE VIO 300; 25 W) or treatment with argon plasma coagulation (ERBE VIO 300; 60 W, 2.0 L/min) will only be performed when remnant tissue in suspected and must be registered.3.*Both arms*

For both procedures length of the procedure will be measured, defined as the total time needed for resection of the polyp, measured from the minute the injection fluid is injected until the endoscopist finishes final inspection of the resection wound and all specimen pieces are collected and removed.

For both procedures the opposite colonic wall of the resection site will be marked with India ink in case the adenoma is located in the sigmoid or descending colon, to ensure that the post-polypectomy scar can be found during follow-up.

For both procedures the following events are considered standard care, however, will be registered. In case intraprocedural perforation occurs, this will be treated using clips. In case of a minor bleeding from a small vessel, contact coagulation with the tip of a knife or coagulation with hemostatic forceps will be used for hemostasis. In cases of a severe bleeding from a large vessel or artery, hemostatic forceps will be used for hemostasis. If a pulsating large vessel is exposed within the resection wound, clipping can optionally be used to prevent delayed bleeding. If overnight admission is required, this will be registered including motivation.

### Handling of the resected specimen

The resected specimen will be pinned on a paraffin, rubber or cork sheet so that the mucous membrane surrounding the lesion is evenly flattened and the mucous membrane surface can be observed, unless fragmentation as a result of piecemeal resection hampers this. In order to prevent autolysis after resection, the specimen must be fixed as quick as possible. To prevent drying, it will be soaked in a formalin solution. Thereafter, the endoscopist is required to appropriately display the specimen so that the difference between the specimen and the clinical images is minimized and the tumor margin of the specimen can be judged. The endoscopists will provide documentation (an explanatory text) to the pathologist so that the basic information on preoperative diagnosis, the site and morphology of the lesion, and the tumor size can be accurately conveyed.

### Histopathological evaluation

The received specimen is fixed with a 4 % buffered formaldehyde solution for 24 h at room temperature. After fixation, the specimen is photographed and inked. A tangent that touches the focus closest to the horizontal tumor margin is assumed. The first cut is carried out in the direction perpendicular to the tangent. The specimen is sectioned into slices at intervals of 2 mm parallel to the first cut. All slices are embedded in cassettes for histological diagnosis. In case of long slices (>2 cm), the slice is cut in half and both halves are embedded after ink is applied at the cut edge.

Histological diagnosis of tumors is carried out in accordance with the Vienna classification of gastrointestinal neoplasia [26]. The histological type and resection tumor margins in mm (horizontal and vertical) of the lesion will be judged. Incomplete (R1) resection is defined as dysplasia infiltration of the margins and/or if infiltration cannot be determined because of coagulation artefacts, as in piecemeal resection.

### Follow-up colonoscopies

A follow-up colonoscopy is performed 6 and 36 months after the procedure for all patients. The post-polypectomy scar is checked for residual disease. In case of macroscopic residual disease this is resected and send for pathology. If not**,** three biopsies of the scar will be taken. If no recurrence is found at the 6-months colonoscopy, the next colonoscopy will be planned at 36 months. Only if recurrence is found at the 6-months colonoscopy, the next follow-up colonoscopy will be planned 6 months later (T = 12 months). This is repeated until no recurrence is found with a maximum of three endoscopic resection attempts before referral to the surgeon. Length of the follow-up colonoscopies will be registered for all time points, measured from the introduction of the scope until the endoscopist finishes final inspection of the postpolypectomy scar (including taking biopsies and/or resection of residual disease).

### Safety monitoring

The investigators will inform the subjects and the reviewing accredited medical ethics committee if anything occurs, on the basis of which it appears that the disadvantages of participation may be significantly greater than was foreseen beforehand. The study will be suspended pending further review by the accredited medical ethics committee, except insofar as suspension would jeopardize the subjects’ health. The investigators will take care that all subjects are kept informed.

Adverse events (AE) are defined according to the complication registration of the Dutch Society of Gastrointestinal Diseases (NVMDL) for non-severe complications [27]. Endoscopic resection related AE’s are: intraprocedural perforation, intraprocedural bleeding, postprocedural bleeding or postprocedural serositis that requires (prolonged) admission <10 days and/or maximum 4 units blood transfusion and/or endoscopic or percutaneous (re-) intervention. Serious adverse events (SAE) are defined as intraprocedural perforation, intraprocedural bleeding, postprocedural bleeding or postprocedural serositis or any other event with a possible or definite causal relation with the study intervention as judged by the treating physician that requires (1) > 10 days (additional) admission and/or (2) 4 units blood transfusion and/or (3) angiographic or surgical intervention and/or, (4) ICU admission and/or (5) death. These SAE’s will be reported to the accredited medical ethical committee of the University Medical Centre Utrecht (UMC Utrecht), within 15 days after the local investigator has first knowledge of the serious adverse events.

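### The AE list omits postprocedural perforation, the AE and SAE cut-offs do not sort events into one class each, and intraprocedural perforation counts as a complication only if it leads to admission or surgery

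*Protocol article*

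**What the plan says.** The Safety monitoring section of the protocol article sets out two tiers. AEs follow a national society's complication registration for non-severe complications and are then listed: "intraprocedural perforation, intraprocedural bleeding, postprocedural bleeding or postprocedural serositis that requires (prolonged) admission <10 days and/or maximum 4 units blood transfusion", with endoscopic or percutaneous (re-)intervention as a further qualifying criterion. SAEs name the same four events and add a catch-all: "or any other event with a possible or definite causal relation with the study intervention as judged by the treating physician". The SAE criteria begin "1) > 10 days (additional) admission and/or (2) 4 units blood transfusion and/or (3) angiographic or surgical intervention" and go on to ICU admission and death. SAEs are reported to the ethics committee within 15 days.

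The complication rate within 30 days is a secondary outcome with its own definitions. Intraprocedural perforation is a visible breach of the wall "because of mural tissue defects, that requires (1) (prolonged) admission or (2) surgery". A fifth event, absent by name from both safety lists, is also defined: "Postprocedural perforation is defined as perforation within 30 days after the procedure that is detected after completing of the procedure". Serositis has similar symptoms "but without signs of perforation (free air at abdominal CT-scan".

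The Trial interventions section, under both arms, states "For both procedures the following events are considered standard care, however, will be registered". The first such event is intraprocedural perforation, to be closed with clips.

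**The concern.** The Background presents perforation as part of the price of ESD: 5.7% against 1.4% with EMR. The rules that decide whether a perforation is recorded as an AE, an SAE or a complication should therefore be complete and agree with each other. They fall short in three ways.

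- One defined type of perforation has no place in the non-severe tier.
- The two tiers neither meet cleanly nor exclude each other. This matters because SAEs carry a reporting deadline, and the Quality control section has monitors check that SAEs are correctly reported.
- Whether an intraprocedural perforation counts in the between-arm comparison depends on what the treating team does next. The team knows the arm. ESD patients from centres without ESD experience are referred to an expert centre, so admission practice could differ by arm for reasons unrelated to the injury.

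**Working it through.** **1. The event lists side by side**

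| Event | Complication rate (Secondary outcomes) | AE list | SAE list |
|---|---|---|---|
| Intraprocedural perforation | yes, if admission, longer stay or surgery | named | named |
| Intraprocedural bleeding | yes, with threshold | named | named |
| Postprocedural bleeding | yes, with threshold | named | named |
| Postprocedural serositis | yes | named | named |
| Postprocedural perforation | yes, no consequence threshold | **not named** | **not named**; catch-all if related and severe |

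A postprocedural perforation cannot be filed as serositis, because that definition requires no sign of perforation. The AE sentence has no catch-all. A case that meets no SAE criterion is therefore in neither class.

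**2. The cut-offs**

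The AE tier takes a stay under 10 days or at most 4 units. The SAE tier takes a stay over 10 days or 4 units, with no comparison sign. Taking these two criteria alone:

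| Stay (days) | Units | AE | SAE, exactly 4 units | SAE, at least 4 units |
|---|---|---|---|---|
| 9 | 0 | yes | no | no |
| 10 | 0 | **no** | **no** | **no** |
| 11 | 0 | no | yes | yes |
| 0 | 3 | yes | no | no |
| 0 | 4 | **yes** | **yes** | **yes** |
| 0 | 5 | no | **no** | yes |
| 11 | 2 | **yes** | **yes** | **yes** |

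Exactly 10 days is a gap and exactly 4 units an overlap. Five units is unclassified or serious, depending on the reading. Because criteria are joined by and/or, 11 days with 2 units meets both definitions.

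**3. A clipped intraprocedural perforation with no admission**

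It is registered (Trial interventions). It is not a complication (Secondary outcomes). It is an AE if clipping counts as endoscopic intervention (Safety monitoring). If the Secondary outcomes definition also governs the AE list, the endoscopic criterion can never bring in a perforation by itself. The sections do not say which applies.

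**4. Scale**

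The arm size comes from the Sample size calculation, which reproduces with unpooled variance: (1.960 + 0.842)² × (0.12 × 0.88 + 0.02 × 0.98) / 0.10² = 98.27, so 99 per arm and 198 in total; 198 × 1.07 = 211.9, so 212, or 106 per arm. Nothing in this point alters that figure.

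Expected perforations at the Background rates:

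- ESD: 106 × 0.057 = 6.04
- EMR: 106 × 0.014 = 1.48

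The share that leads to admission or surgery is not given. With the same assumed share in both arms:

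| Share counted | ESD | EMR |
|---|---|---|
| 100% | 6.0 | 1.5 |
| 75% | 4.5 | 1.1 |
| 50% | 3.0 | 0.7 |
| 25% | 1.5 | 0.4 |

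The shares need not be equal. With every event counted, the difference is 6.04 − 1.48 = 4.56 events. With all ESD and half of EMR events counted, it is 6.04 − 0.74 = 5.30. With half of ESD and all EMR events counted, it is 3.02 − 1.48 = 1.54. The distortion can go either way.

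Power for 5.7% against 1.4% with 106 per arm (two-sided 0.05, pooled variance under the null):

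- Null standard error: √(2 × 0.0355 × 0.9645 / 106) = 0.0254
- Alternative standard error: √((0.057 × 0.943 + 0.014 × 0.986) / 106) = 0.0252
- z = (0.043 − 1.960 × 0.0254) / 0.0252 ≈ −0.27, so power is about 39%

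With so few events, a change of two or three alters the picture.

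**The case against.** A reader might infer that delayed perforation escapes safety reporting or drops out of the comparison. The protocol does not support this. The SAE catch-all takes in any related event that meets a severity criterion, so a postprocedural perforation leading to surgery, ICU care, death or a stay over 10 days is an SAE as written. Delayed perforation is also in the complication rate, with no admission condition, and that rate is what the Data analysis section compares. No analysis in the article uses the AE/SAE split. This part of the objection stands and confines the omission to the non-severe tier. The AE definition also leans on an outside registration that is not available here and may cover the missing event, although the article goes on to print its own list.

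A reader might also infer that ESD's perforations will be undercounted relative to EMR's. That is not shown. The condition applies in both arms, and if ESD patients are admitted more readily it keeps ESD events preferentially. The 6.0 is probably generous: the Background says complications are fewer in the distal colon, and it does not say whether 5.7% mixes intraprocedural and delayed events.

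Finally, it can be argued that a consequence threshold is a legitimate, prespecified choice, applied to both bleeding outcomes too, and that the cut-off faults are slips of wording. Both are fair. The threshold still makes the count depend on unblinded management decisions and sits awkwardly with the AE criterion. The slips still leave boundary events without a single class. Since every intraprocedural perforation is registered, nothing is lost from the data; the issue is what gets reported.

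**Conclusion.** The point holds in a limited form. A non-severe postprocedural perforation has no class in the printed safety definitions, and the admission and transfusion cut-offs do not partition events. These faults affect safety classification and reporting, not the comparison of arms.

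Only the condition on intraprocedural perforation touches the comparison. It makes a secondary safety outcome depend on admission decisions by clinicians who know the arm. The possible scale runs from 6.0 vs 1.5 counted events down to 1.5 vs 0.4. This rests on the Background rates applying to this population, all those perforations being intraprocedural, and an assumed 100% to 25% meeting the condition equally in both arms. The protocol gives neither the true share nor the direction of any bias. The primary endpoint and sample size are unaffected.

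**What to change.** Three changes of wording and reporting:

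1. Name postprocedural perforation in the AE and SAE lists. For SAEs this only makes explicit what the catch-all covers when the event is severe and related.
2. Reconcile the admission and transfusion cut-offs, and state what happens when an event meets criteria from both tiers, so that each event falls in exactly one class. Where the lines fall is for the trial team to decide.
3. Keep the complication rate as defined, and beside it report by arm every registered intraprocedural perforation, with its consequence (none, admission, surgery) as a severity grade. State whether clipping alone makes a perforation an AE.

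No new data are needed for the third change, because these events are already registered, and no change touches treatment. The cost is redrafting, plus a reported perforation rate that may look slightly less favourable than the conditional one.
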